**Figure 1 figure1:**
[figure not shown]
The timeline of the CBT-I (cognitive behavioral therapy for insomnia) intervention.

**Figure 2 figure2:**
[figure not shown]
The timeline of Health Education.

##### Experimental Intervention

Participants allocated to the CBT-I group will meet with the CBT-I provider weekly for 1 hour of CBT-I sessions. CBT-I is designed to address cognitive and behavioral factors that perpetuate insomnia [102]. It includes several therapeutic components including sleep restriction therapy, stimulus control therapy, sleep hygiene, relaxation techniques, and cognitive therapy. At each session, the CBT-I provider will ask about any new difficulties, explain the outline of the session, calculate the SE of the previous 7 nights of sleep, and close the session with assessing any concerns and providing a new sleep diary. At each session, prescribed time in bed and out of bed will be determined based on calculation for SE of the weekly sleep diary. SE will be calculated as the ratio of TST and total bed time multiplied by 100. At each session, if the SE is greater than 90%, participants will be given the opportunity to go to bed 15 min earlier. If SE is between 85% and 89.9%, participants will be asked to remain on the same sleep schedule as currently prescribed. If it is less than 85%, they will be asked to move their bedtime 15 min later, although total time in bed will not be less than 6 hours.

This protocol intervention was designed based on a session-by-session guide [103].

###### Session 1 (60-90 Min)

Sleep restriction therapy, stimulus control therapy, and sleep hygiene will be started in this session. The sleep diary from the previous week will be reviewed to calculate the average SE from the previous 7 nights. In this session, subjects will learn the rationale and efficacy of using sleep restriction therapy and stimulus control therapy as a first line of treatment. Sleep restriction therapy is designed for individuals who are not able to initiate and/or maintain sleep [103,104]. This technique limits the time in bed to be equivalent to the TST by identifying the wake time and TST to increase the SE. Stimulus control promotes sleep drive and reinforces circadian entrainment by associating the bed to sleep only or for sex [103,104]. By applying the sleep restriction and stimulus control interventions, we will set prescribed time in bed and prescribed time out of bed by using the average of TST from previous week sleep diary and preferred time to wake up in the morning. Thus, the goal of this session is to align sleep with the opportunity to sleep, make plan in staying awake until the prescribed time in bed for sleep restriction therapy, and provide a list of activities during awake time or WASO for stimulus control therapy. In addition, sleep hygiene is implemented to minimize the influence of negative behaviors on sleep quality and quantity [103,104]. Sleep hygiene focuses on the impacts that diet, exercise, caffeine, alcohol, and environment can have on sleep [103,104].

###### Session 2 (30-60 Min)

Sleep titration, reviewing sleep hygiene, and introducing diaphragmatic breathing technique will be covered in this session. In this week, we will again review the sleep diary to confirm any necessary sleep titration (that is sleep restriction therapy adjustment). Sleep titration will be determined by measuring the individual’s SE. An SE >90% indicates positive gain that directs upward sleep opportunity. An SE between 85% and 90% score indicates marginal gain that maintains the sleep schedule. An SE <85% score indicates negative gain that directs downward sleep opportunity. If compliance issues arise during the sleep diary review, this session will focus on reinforcing the importance of sleep restriction and stimulus control therapies. Stress and anxiety symptoms are commonly reported in people with insomnia [105]. Thus, it is also important to implement relaxation techniques at the first sessions. We will emphasis relaxation therapy for people who are not able to relax because of varied of stressors or being an anxious. One of the relaxation therapies is the diaphragmatic breathing technique that promotes muscle relaxation, breathing performance, and memory relaxation. A brief diaphragmatic breathing handout and video will be utilized during the session.

###### Session 3 (30-60 Min)

Similar to sessions 1 and 2, the sleep diary will be reviewed for sleep titration, and we will introduce mindfulness. Upward or downward sleep titration will be determined based on the sleep diary. Mindfulness has shown positive effects in reducing cognitive and somatic arousal when combined with CBT-I for people with insomnia [106]. The principles of mindfulness (nonjudging, patience, trust, acceptance, and letting go) and its practice will also be introduced during this session.

###### Session 4 (30-60 Min)

Sleep titration and progressive muscle relaxation will be delivered in this session. Upward or downward sleep titration will be determined based on the sleep diary. Muscle relaxation therapy is a physiological intervention designed to measure and reduce muscle tension [107]. In addition, muscle relaxation therapy has been incorporated with CBT-I to improve insomnia and depression symptoms [107]. A brief progressive muscle relaxation handout and video will be utilized during the session.

###### Session 5 (30-60 Min)

Sleep titration and cognitive therapy will be delivered in this session. Cognitive therapy is designed to change detrimental beliefs and attitudes about sleep. The intervention content provided in sessions 1, 2, 3, or 4 may be similar to the cognitive therapy provided in session 5, although session 5 will focus on providing the cognitive therapy intervention in its entirety. During this session, we will work on reducing sleep effort, catastrophizing, anxiety about sleep, and insomnia relapse. Also, we will work on correcting negative sleep beliefs, particularly regarding insomnia. In addition, we will work on enhancing individuals’ willingness to modify the sleep-related behaviors and engage in good strategies. Finally, we will continue working on sleep titration to optimize the SE.

###### Session 6 (30 Min)

Assessing global treatment gains and relapse prevention education will be the focus in this session. We will review the SE of each session to graphically demonstrate the participant’s SE over the course of this intervention. This process will help in providing information that facilitates chronic insomnia and understands the risk factors of reoccurrence. Finally, we will discuss the approaches to maintain clinical gains and fix insomnia returns, and we will schedule participants for the reassessment session.

During each session, the CBT-I provider will use 2 documentation sheets that are nonspecific to CBT-I: a checklist and tracking sheet. These sheets will help the CBT-I provider for quality assurance and standardization of treatment sessions across participants. We do not expect these sheets to contribute to the intervention or the outcomes of this study.

The participants will be called 1 day before each session to confirm their session appointment the following day and remind them to bring their completed sleep diary. In addition, a folder will be provided at the first session to keep provided materials together for review. The CBT-I sessions will be audio recorded to assess treatment integrity if the subject agrees.

CBT-I intervention fidelity will be assessed by an independent CBT-I expert who will use a scoring sheet to assess CBT-I provider’s compliance in utilizing the manual to deliver the CBT-I. The CBT-I provider will be scored on 5 scales from 0 (poor) to 6 (excellent) based on (1) how they address immediate concern, (2) how they explain the outline of the session, (3) how they discuss the sleep diary outcomes, (4) their adherence in providing the intervention, and (5) their competency in delivering each session.

##### Control Group

Participants allocated to the HE group will meet with the CBT-I provider weekly for 1 hour of HE sessions. The HE sessions include several components including brief sleep hygiene, foot care, diabetes classifications, healthy diet, and physical activity. During all sessions, subjects will be encouraged to engage in discussion through open questions about their experience of diabetes and lifestyle as well as their comprehension of the provided materials. Similar to the CBT-I group, session tracking sheets will be used to track new difficulties or concerns and provided education.

#### Outcomes

##### Demographic and Clinical Variables

Age, race, ethnicity, sex, marital status, education, employment, diabetes duration, medication list, and body mass index will be gathered at the first assessment session.

##### Sleep Outcomes

###### Insomnia Severity

The Insomnia Severity Index (ISI) is a self-report measure designed to evaluate the nature, severity, and impact of insomnia [108]. The ISI is a valid and reliable measure of clinical insomnia and involves 7 questions, each rated on a 0 to 4 Likert scale. Total scores range from 0 to 28, with higher scores indicating greater insomnia severity [108]. The internal consistency of ISI was excellent for community sample and clinical sample (alpha=.90 and alpha=.91, respectively). The cutoff score>10 on the ISI provided optimal sensitivity and specificity for the detection of insomnia based on the Diagnostic and Statistical Manual of Mental Disorders, fifth edition, diagnostic criteria (area under the curve=0.82; 95% confidence interval 0.78-0.86) [109].

###### Sleep Variability

The Actigraph device is a small, noninvasive device worn on the nondominant wrist that records limb movements using electrical impulses, and it has been validated for use in people with insomnia [110]. Sleep parameters including SE, SL, TST, and WASO will be measured. In addition to the Actigraph, we will also use a sleep diary to allow for better estimation of the time in and out of bed as well as for removing invalid sleep periods that are measured by the Actigraph [111]. The sleep diary will also measure total time spent in bed, total time spent out of bed, number of awakenings, number of bathroom visits, and glucose level before and after sleep time. All sleep parameters will be presented in averages of 7 nights and the coefficient of variance (CV) will be calculated using the following equation (CV=standard deviation/mean×100) for each objective and subjective sleep parameters—SE, SL, TST, and WASO—to analyze objectively within-subject variability of nighttime sleep of 7 nights. This calculation will provide a percentage value with a higher number suggesting higher variability [112].

###### Daytime Sleepiness

The Epworth Sleepiness Scale (ESS) uses 8 items on a 4-point Likert scale, where the subjects rate how likely they would be to fall asleep in 8 different states of daily activities. The ESS has demonstrated satisfactory psychometric properties such as test-retest reliability (r=.82) and internal consistency (alpha=.88). The cutoff point is ≥10 to distinguish between normal from pathological sleepiness [24].

###### Sleep Quality

The Pittsburgh Sleep Quality Index (PSQI) is a validated 19-item questionnaire that differentiates between poor and good sleepers. The PSQI uses 7 items on a 4-point Likert scale, and it yields a global sleep quality score that ranges from 0 to 21. Poor sleepers have scores >5, with this cutoff global PSQI score providing satisfactory sensitivity (89.6%) and specificity (86.5%). In our study, we will use a 3-factor scoring model for the PSQI (SE, perceived sleep quality, and daily disturbances), which has been tested and validated [113]. Sleep duration and SE were classified under the SE factor; subjective sleep quality, SL, and the use of sleeping medications were categorized under the perceived sleep quality factor; and the frequency of sleep disturbances and daytime dysfunction were classified under the daily disturbances factor.

##### Diabetes Outcomes

###### Diabetes Self-Care Behavior

The diabetic care profile (DCP) uses items on 5-point Likert scales to evaluate the frequency of symptoms related to diabetes. The DCP is a validated instrument that measures self-reported diabetes control and psychological and social factors associated with the management of diabetes [114,115].

###### Glycemic Control

A_1c_ will be determined using the hemoglobin A_1c_ test by a disposable blood finger stick test using (A1cNow+ kit; TMS Company). The A_1c_ indicates the average blood glucose level of people with diabetes over the previous 2 to 3 months and represents the current management of diabetes [116]. Every 1% drop in A_1c_ is associated with improved outcomes with no threshold effect [117].

###### Glucose Level

Random glucose levels will be measured using glucose meter (Contour Next EZ Blood Glucose Monitoring System, Model 7252). The results of glucose level will be presented in milligrams per deciliter to document nonfasting glucose levels [118].

##### Health Outcomes

###### Fatigue Severity

Fatigue symptoms will be measured using the Fatigue Severity Scale (FSS), which is a 9-item questionnaire that has been validated in people with diabetes [119]. The FSS measures fatigue across 5 subscales including motivation, exercise, interference with work, family, or social life. These subscales have total scores where a score <4 indicates no fatigue, scores between 4 and 4.9 indicate moderate fatigue, and a score >5 indicates severe fatigue [119].

###### Pain Severity Symptoms

The BPI is a valid and reliable measure to assess painful diabetic peripheral neuropathy [120]. We measured the means of the severity scale and the interference scale of the BPI.

###### Depression Symptoms

The BDI has high reliability and good validity [121,122]. It contains 21 self-reported items on a 3-point Likert scale, with scores ≥21 indicating severe depression symptoms [121,122].

###### Anxiety Symptoms

The GAD-7 uses 7 items on a 3-point Likert scale. The total score of the GAD-7 ranges from 0 to 21, with higher scores indicating severe anxiety symptoms. It has been shown to be highly sensitive and specific for the detection of anxiety symptoms, and it is correlated with other anxiety scales [123].

### Participant Timeline

All measurements will be performed at baseline and 1 week after treatment completion (Figure 3). Participants who wish to withdraw during the intervention will be asked to complete the reassessment session.

At initial contact with a potential subject, a phone screening or diabetes clinic interview will be conducted by a member of the research team to determine whether an individual qualifies to progress to an in-person screening for the study. The phone screening interview assesses participant eligibility according to age, self-report of T2D diagnosis, insomnia severity, ability to understand English, STOP-Bang score, RLS Diagnostic Index, pregnancy status, alcohol use, night-shift work, and undiagnosed neurological disorders.

Individuals passing the phone screening will be scheduled for an in-person screening session to assess eligibility according to symptoms of pain, depression, and anxiety.

Subjects will undergo the consent process in a private room at KUMC before completing any of the in-person screening assessments. Individuals passing the in-person screening will then immediately begin baseline assessment.

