**Methods:**

This RCT will use random mixed block size randomization with stratification to assign 28 participants with T2D and insomnia symptoms to either a CBT-I group or a health education group. Outcomes including insomnia severity; sleep variability; diabetes self-care behavior (DSCB); glycemic control (A_1c_); glucose level; sleep quality; daytime sleepiness; and symptoms of depression, anxiety, and pain will be gathered before and after the 6-week intervention. Chi-square and independent *t* tests will be used to test for between-group differences at baseline. Independent *t* tests will be used to examine the effect of the CBT-I intervention on change score means for insomnia severity, sleep variability, DSCB, A_1c_, fatigue, sleep quality, daytime sleepiness, and severity of depression, anxiety, and pain. For all analyses, alpha level will be set at .05.

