In addition, during the phone screening, we will exclude the following people: 1) Those with scores >4 on Stop Bang items including snoring, tiredness, observed apnea, blood pressure, body mass index, age, neck circumference, and gender. People with sleep apnea symptoms commonly report poor sleep quality and insomnia [68]. The Snoring, Tiredness, Observed apnea, Blood pressure, Body mass index, Age, Neck circumference, and Gender (STOP Bang) questionnaire will be used to screen the common symptoms related to the high risk of sleep apnea, such as the presence of snoring behavior, wake time sleepiness or fatigue, and history of obesity or hypertension [69]. Neck circumference will be measured in the active screening session. STOP Bang showed higher sensitivity and specificity (93% and 28%, respectively), compared with other screening questionnaires at polysomnography-derived apnea-hypopnea index (score of 15), which indicates severe sleep apnea [70]. In addition, a meta-analysis [71] recommended using the STOP-Bang questionnaire as a screening for sleep apnea. If interested subjects have positive scores for 5 or more categories, they are classified as being at high risk of sleep apnea [69]. Those subjects will be excluded and recommended to visit their sleep specialists. We expect some people are diagnosed with sleep apnea and they are adhered with their CPAP machine. Those people will be still included by asking them to answer the STOP Bang questionnaire with considering CPAP utilization; 2) those failing to pass the RLS Diagnostic Index [72]. The RLS Diagnostic Index is based on an algorithm to give yes or no conclusion regarding the presence of RLS. The RLS Diagnostic Index includes questions about the urge to move legs or arms to detect the risk of RLS symptoms [72]. If the RLS Diagnostic Index indicates higher RLS risk, individuals *fail* the RLS Diagnostic Index, as RLS has a negative impact on individuals’ sleep, specifically, insomnia [73]; 3) those who are pregnant. As pregnancy impacts sleep, and insomnia is one of the major problems experienced in pregnancy, individuals who are pregnant will be excluded to reduce potential confounding factors [74]; 4) those who are heavy alcohol drinkers. In accordance with definitions established by the National Institute of Alcohol Abuse and Alcoholism [75], heavy drinking is typically defined as consuming 15 drinks or more per week for men and 8 drinks or more per week for women. Heavy alcohol consumption has been shown to be associated with sleep complaints among adults [76]. In addition, heavy drinking has been shown to be associated with subsequent insomnia symptoms in adults aged between 40 and 60 years [76]. Therefore, heavy alcohol drinkers will be excluded to reduce potential confounding factors; 5) those having any of the following self-reported problems: Neurological diseases—people with previous neurological disorders (eg, multiple sclerosis, Alzheimer disease, Parkinson disease, traumatic brain injury, and stroke—people with these neurological disorders usually report sleep problems [77-81]. Therefore, we want to focus on the interaction between insomnia and T2D; bipolar and seizure disorders—people with bipolar disorder and seizure disorder have complex sleep problems other than insomnia [82,83]. Furthermore, CBT-I is contraindicated for these populations [84]; chronic fatigue syndrome, fibromyalgia, and rheumatic diseases—people chronic fatigue syndrome is a medically unexplained disabling illness with nonrestorative sleep and potentially extended sleep duration [85]. Pain, fatigue, and poor sleep quality are common symptoms in people with fibromyalgia and rheumatic diseases [86-90]. Therefore, people with chronic fatigue syndrome, fibromyalgia, or rheumatic diseases will be excluded in this study; and dialysis, blindness, and transfemoral amputation—these diabetes complications may restrict people with T2D from performing components related to CBT-I; and 6) those who are shift workers. Shift workers usually report more physical and psychological distress, insomnia, and stress than non–shift workers [91]. In addition, CBT-I is contraindicated for people with shift work because CBT-I might increase sleepiness, which could put the individual at increased risk of harm.

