#### Data Collection, Management, and Analysis

##### Data Collection and Methods

Insomnia severity (primary outcome); sleep variability; fatigue; DSCB; A_1c_; daytime sleepiness; sleep quality; glucose levels; and symptoms of depression, anxiety, and pain will be measured a week before and after the intervention.

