###### Harms

During the pre and postassessment sessions, testing will be stopped if the subjects show signs of low blood sugar (<70 mg/dL) or if signs of dizziness or headache are noted by the assessor or reported by the participant. During assessment sessions, participants also will be instructed to stop the test at any time for a rest break, as often as needed.

There is a risk of skin redness may be associated with wearing the Actigraph for 1 week. The risks of wearing the Actigraph are nearly the same as wearing a wrist watch. If skin redness or inflammation happened, subjects may remove the Actigraph and immediately report the symptoms to research personnel. In addition, there is a risk of minor electrical shock if the Actigraph is damaged. If damage to the Actigraph occurs, subject will be asked to return it to our lab, and they will be given a replacement.

Initially, participating in a CBT-I intervention may have an increase in sleepiness, which may impact participants’ fatigue, thinking ability, or functional abilities. It is anticipated that this increase in sleepiness will be temporary and should help participants sleep better in the long term.

During the in-person screening session, if suicidal intent is identified through either the BDI (question number 9, with a *2* or a *3*) or verbal statement from the participant, a suicidality protocol will be followed. The suicidality protocol is designed to provide the researcher with contact information for appropriate psychology and psychiatric professionals at KUMC.

####### Research Ethics Approval

The study will be performed in accordance with KUMC’s Institutional Review Board and Human Subjects Committee. No individuals will be excluded based on sex, race, or ethnicity. Interested participants will be administered a structured screening interview to determine their eligibility for the study. During the consent session, all interested participant will be informed about the study’s objective, risks, procedure, and potential benefits (or lack thereof).

######## Consent or Assent

Consent will be obtained in Georgia Holland Health Exercise and Aging Lab on the main campus of KUMC. Participants will be encouraged to ask any questions about the study as much as they need, and members of research study will answer their questions. In addition, participants will be informed if there is any change in the protocol to sign a new consent form.

######## Confidentiality

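### The early, temporary sleepiness that the plan expects from CBT-I is not scored on any scale while it can occur

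*Protocol article*

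**What the plan says.** The protocol article's Harms section warns: "Initially, participating in a CBT-I intervention may have an increase in sleepiness, which may impact participants’ fatigue, thinking ability, or functional abilities". It adds that the rise should be temporary. The other risks listed there come from the assessments or the Actigraph, so this is the one harm attributed to the treatment. The eligibility text takes the same effect seriously when it explains why shift workers are excluded: "CBT-I might increase sleepiness, which could put the individual at increased risk of harm".

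The Daytime Sleepiness section names one instrument: "The Epworth Sleepiness Scale (ESS) uses 8 items on a 4-point Likert scale". It gives 10 or more as the cutoff for pathological sleepiness.

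Timing is stated three times, consistently. Participant Timeline: "All measurements will be performed at baseline and 1 week after treatment completion". Data Collection and Methods, whose list includes daytime sleepiness: "will be measured a week before and after the intervention". The abstract's Methods: "will be gathered before and after the 6-week intervention".

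Sessions are weekly for 6 weeks in both arms. Sleep restriction starts in session 1, and later adjustment depends on sleep efficiency from the diary: "If it is less than 85%, they will be asked to move their bedtime 15 min later", subject to a 6-hour floor on time in bed.

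**The concern.** A harm described as initial and temporary is scored only before it can begin and after treatment has ended. A pre-post change score suits a lasting effect. It says little about a rise that comes and goes in between.

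The evidence is also one-sided. Objectives and Hypotheses predicts that daytime sleepiness will improve more with CBT-I than with health education. The two time points can show that benefit, but they may leave no trace of the worsening that the Harms section predicts. The Discussion's Overview anticipates that, if results are favourable, CBT-I could be put into practice as a safe as well as an effective treatment for this population. On this schedule, the statement about safety would have no scored on-treatment data on the one treatment harm named.

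**Working it through.** The plan states no figure to reproduce. The check lays out the stated schedule and then looks for any other record of sleepiness during treatment.

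**Schedule**

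Inputs: baseline a week before the intervention (Data Collection and Methods); 6 sessions, one per week (Interventions); reassessment 1 week after treatment completion (Participant Timeline), taken here as 1 week after session 6; restriction from session 1 (Session 1).

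- Baseline ESS: day 0.
- Session k: day 7 + 7 × (k − 1), giving days 7, 14, 21, 28, 35 and 42.
- Post-treatment ESS: day 42 + 7 = day 49.
- ESS dates: days 0 and 49. Number falling between day 7 and day 42: **0**.
- Time from the start of restriction to the next ESS: 49 − 7 = **42 days, about 6 weeks**.

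The count of 0 does not depend on the exact gap between baseline and session 1. It follows from having one assessment before session 1 and one after session 6.

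**Other possible sources during treatment**

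| Source | Where described | Scores daytime sleepiness? |
|---|---|---|
| Open question on problems, and a closing check on concerns, each CBT-I session | Experimental Intervention | No item or scale named |
| Checklist and tracking sheet, each CBT-I session | Session 6 | Contents not given; described as quality assurance and standardization |
| Tracking sheets for difficulties and concerns, health education | Control Group | No item or scale named |
| Sleep diary | Sleep Variability | Listed contents are bed times, awakenings, bathroom visits and glucose, with sleep parameters; daytime sleepiness is not listed |

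Statistical Methods analyses change scores, including one for daytime sleepiness. It does not use the tracking sheets or any on-treatment sleepiness record.

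**Entry criteria**

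The eligibility lists set no upper limit on the ESS. Some participants may already be at or above 10 at baseline, so a bare count of scores of 10 or more would mix existing with new sleepiness. This shapes the fix.

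**The case against.** The strongest reply is that nothing here is contradictory. A before-and-after ESS matches the stated hypothesis and analysis, and the timing sentence governs outcome assessments rather than the capture of harms. It cannot be wholly literal in any case, since diaries are collected weekly. Harms have their own route: participants in the CBT-I arm are asked about problems and concerns at every session, both arms have tracking sheets, and CBT-I sessions are audio recorded with agreement. This is also a journal article, the sheets themselves are not shown, and a fuller protocol may hold adverse-event forms.

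Much of this stands. Sleepiness could be volunteered and written down, so a claim that it cannot be detected at all would be wrong. What remains is that the article itself fixes the only sleepiness scale at two time points, in three places that agree. The on-treatment record it describes is unscored, is taken by an unblinded provider and enters no stated analysis.

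Three stronger readings are tempting, but the text does not carry them:

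- **A reader might infer that the sleepiness will have gone by reassessment.** The Harms section gives no duration. It could have resolved by then, and no more can be said.
- **A reader might infer that people who leave because of sleepiness are lost to the post-treatment ESS.** Participant Timeline says that those who withdraw will be asked to complete reassessment, and Statistical Methods plans a completer versus noncompleter analysis. Nothing in the document links withdrawal to sleepiness.
- **A reader might try to size the harm by adding up the 15-minute bedtime shifts.** The general rule applies at each session, but the description of session 6 lists no titration, and the 6-hour floor may stop the shifts earlier. A sum would not measure sleepiness anyway.

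**Conclusion.** The point holds as a gap in measurement timing and should be corrected; it is not a contradiction in the plan. The one treatment harm named has 0 scored assessments between sessions 1 and 6, and the next ESS comes about 6 weeks after restriction starts. The pre-post ESS can serve as an efficacy measure. It may miss a transient worsening, and it cannot by itself support a conclusion that CBT-I is safe.

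This rests on taking the three timing statements as they are written, and on the tracking sheets and checklist holding no sleepiness scale, since none is described. If those sheets do carry a scored sleepiness item, the gap narrows to the absence of a stated analysis. The documents do not allow an estimate of how many participants would be affected or by how much.

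**What to change.** In Daytime Sleepiness, Participant Timeline, and Data Collection and Methods, add the self-completed ESS at each weekly session in both arms. If the form is filled in before session 1 starts, that value is a second pre-treatment reading, and sessions 2 to 6 give 6 − 1 = 5 on-treatment readings.

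Report by arm:

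- the on-treatment change from baseline, week by week;
- the highest on-treatment score;
- the number newly reaching the plan's cutoff of 10, among those below it at baseline.

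Keep the post-treatment ESS as the efficacy measure. Any clinical response to a high score is for the investigators to decide.

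The article reports that recruitment and the study finished in September 2019, so weekly collection may no longer be possible for this cohort. In that case, state that sleepiness was not scored during treatment, summarise tracking-sheet reports of sleepiness by arm, and rest no safety conclusion on the pre-post ESS.

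The cost is a few minutes per session for an 8-item form and some extra data entry. Both arms already attend weekly, so no visits are added.
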